### Sample size calculation

The sample size of this study (41 participants per group) is sufficient to detect a change of 1.0 ± 1.48 points in the score of the Short Physical Performance Battery SPPB [32] with a statistical power of 80% and a significance level of 5%, considering a possible sample loss of up to 15%.

### Statistical analysis

The comparison between groups on tests involving continuous variables (lower limbs functionality, physiological risk of falls, functional performance, quality of life and physical activity level) will be performed using linear models (General Linear Models-ANCOVA) adjusted for baseline values. The rate of falls will be compared between groups using negative binomial regression. Logistic regression models will be used to compare dichotomous variables between groups. All analyses will use the principle of intention-to- treat, in that participants will be analyzed according to their randomized assignment, regardless of whether they complied with the study protocol.

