## Methods

### Trial design

This is a randomized controlled trial with 12 months follow-up. The Ethics Committee on Human Research of the City University of São Paulo (CAAE: 27398814.7.0000.0064) approved the project. This study has been registered with the number protocol of NTC02295527 trials register.

After the baseline assessment an independent investigator, not involved with recruitment or data collection, will randomly allocate the eligible participants to one of two parallel groups by opening a sealed envelope with study group assignments i.e., a concealed allocation system. The randomization schedule will be prepared in advance by an independent investigator, not involved with recruitment or data collection, using in randomly-ordered blocks of 2, 4, and 6 participants. All assessors will be blinded to the group allocation, however, due to the trial design, participants and therapist are not able to be blinded to group allocation.

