### Outcomes

All participants will be assessed in their homes at four different timepoints: at baseline and after 3, 6 and 12 months of randomization.

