#### Primary outcomes

Lower limb functionality will be measured by the Short Physical Performance Battery (SPPB) [20], that consists of three tests that assess static balance, walking speed and, indirectly, the strength of the lower limbs (sitting and standing from a chair unassisted). Each test has a score of zero (worst performance) to 4 points (best performance), totaling a maximum final score of 12 points. This instrument can predict negative consequences such as falls and the onset of disability in older people [21]. The use of walking aids will be allowed during the test if necessary.

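### Baseline-adjusted ANCOVA is the only model named for SPPB, so participants lost before 12 months add nothing to the 12-month contrast even when they have 3- and 6-month scores

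*Protocol article*

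**What the plan says.** - **Visits.** Under Outcomes, all participants are assessed at home "at baseline and after 3, 6 and 12 months of randomization". SPPB is the primary outcome. No visit is singled out as primary for it.
- **Model.** Under Statistical analysis, comparisons of lower-limb function and the other continuous outcomes "will be performed using linear models (General Linear Models-ANCOVA) adjusted for baseline values". No repeated-measures term is named. Dichotomous outcomes go to logistic regression and the rate of falls to negative binomial regression.
- **Analysis principle.** The same section defines intention-to-treat: "participants will be analyzed according to their randomized assignment, regardless of whether they complied with the study protocol".
- **Expected loss.** Under Sample size calculation, 41 per group is said to be enough to "detect a change of 1.0 ± 1.48 points" on SPPB with 80% power at the 5% level, "considering a possible sample loss of up to 15" per cent.

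**The concern.** The design collects three follow-up SPPB scores per participant, and the named model uses one at a time. A participant seen at 3 and 6 months but not at 12 has told us a good deal about the likely 12-month score, and an ANCOVA of the 12-month scores discards that information. This matters if people leave according to how they were doing, and do so differently in the two arms.

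Such a difference is conceivable. Treatment is unblinded. The intervention arm has 18 physiotherapist sessions and adherence calls, while controls have usual care, a booklet and monthly falls calls. At stake is the accuracy of the 12-month effect, not the power of the trial.

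**Working it through.** **1. The plan's own figure.** Inputs from Sample size calculation: difference 1.0, SD 1.48, power 80%, 5% level (two-sided assumed), loss 15%.

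n per arm = 2 × (1.960 + 0.842)² × (1.48/1.0)² = 2 × 7.849 × 2.190 = 34.4, so 35. Inflated: 35/0.85 = 41.2 (rounded up, 42), or 35 × 1.15 = 40.25 (rounded up, 41). The stated 41 is reproduced.

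**2. Who is left out, and power.** Expected losses: 0.15 × 82 = 12.3, about 12 people. Remaining per arm: 0.85 × 41 = 34.85, about 35. Power with 35 per arm is 80.7% (normal) or 79.6% (t), before any gain from baseline adjustment. With an assumed baseline correlation of 0.3, 0.5 or 0.7, adjustment raises it to 84%, 90% or 98%. The planned loss is covered.

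**3. What the intention-to-treat sentence settles.** It keeps a non-complier who has an outcome in the randomised arm, and ANCOVA respects that. It does not say what happens to a participant who has no outcome.

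**4. How bias arises.** Suppose loss after 6 months depends on the 6-month score. Let d be the baseline-adjusted difference between arms (intervention minus control) that selection creates among those who stay, over and above the true effect, in the 6-month score. With equal SDs and a common correlation ρ between visits:

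bias at 12 months ≈ d × ρ/(1 + ρ)

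The multiplier is 0.5/1.5 = 0.33 at ρ = 0.5 and 0.7/1.7 = 0.41 at ρ = 0.7. If both arms select equally relative to their own mean, d = 0 and there is no bias.

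**5. Size by simulation.** 41 per arm, true effect 1.0, total SD 1.48, 4,000 trials per row, loss depending on the 6-month score. The correlations and loss patterns are assumptions. Monte Carlo error is about 0.31/√4000 = 0.005.

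| Assumed loss | ρ | Missing | ANCOVA mean (bias) | Using 3- and 6-month scores | SD of the two estimates |
|---|---|---|---|---|---|
| One rule on the raw score in both arms | 0.5 | 18.4% | 0.963 (−0.037) | 0.997 | 0.311 / 0.310 |
| Same | 0.7 | 18.4% | 0.968 (−0.032) | 0.998 | 0.260 / 0.256 |
| Low-scoring controls leave, intervention at random | 0.5 | 15.9% | 0.920 (−0.080) | 1.000 | 0.310 / 0.309 |
| Same | 0.7 | 15.7% | 0.934 (−0.066) | 1.000 | 0.254 / 0.250 |

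The first pattern leaves a small bias because one rule on the raw score removes more controls, whose mean is 1.0 lower. In the second pattern the bias is about a quarter of a standard error (0.080/0.310 = 0.26; 0.066/0.254 = 0.26). By the formula it corresponds to d of −0.080/0.333 = −0.24 and −0.066/0.412 = −0.16 points.

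Further runs at about 15% to 17% missing:
- Random loss, or the same pattern relative to each arm's mean: bias about 0.
- Low-scoring controls leave: −0.05 to −0.07 (ρ 0.5 to 0.8) and, in a variant, −0.03 to −0.11 (ρ 0.6 to 0.8).
- Low-scoring controls and high-scoring intervention participants leave: −0.10 to −0.14 and, in the variant, −0.07 to −0.22.
- The estimator that also uses the 3- and 6-month scores stayed within about 0.01 of the truth.

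The sign comes from the assumption. If the roles of the arms are exchanged relative to their own means, the bias turns upward by the same amount.

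**6. Fallers.** The proportion of fallers is compared at 6 and 12 months. Plain logistic regression has no place for partial follow-up, so someone lost early without a fall must be dropped or counted as a non-faller.

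**The case against.** Baseline-adjusted ANCOVA is a standard and valid analysis for a two-arm trial. The article does not say that it is fitted visit by visit, does not say that participants with a missing visit are excluded, and does not rule out imputation beforehand. Handling of missing data is commonly left to a full protocol or analysis plan, and neither is shown. All of that stands, so silence about missing data is not the point made here. The point is that the one model the article does fix is not the best fit to its repeated-visit design.

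Stronger readings that a reader might infer, and why the text does not bear them out:
- **That this is a completers' analysis and the intention-to-treat claim fails.** By the article's own definition the claim is met, because non-compliers with an outcome stay in their arm. The accurate term is available-case analysis. The 15% is a sample-size allowance, not an exclusion rule.
- **That the 3- and 6-month data are ignored.** Fitted at each visit, ANCOVA analyses them in their own comparisons. They are only not used towards the 12-month one.
- **That the bias could reach 0.3 points.** Treating 1.48 as the SD left after baseline adjustment gives −0.14 to −0.31. Nothing in the article says it is a residual SD, and the stated sample size is reproduced by an unadjusted comparison with SD 1.48.
- **That loss will differ by arm.** The article gives no data on this. Everyone is assessed at home and both arms are telephoned monthly, which may limit it.
- **That the falls model lacks exposure time.** A rate already implies it, and the offset is detail for an analysis plan.

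It is also fair to say that the near-zero bias of the fuller estimator is built into the simulation, because loss was made to depend only on an observed score.

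**Conclusion.** The concern holds as a worthwhile improvement to the stated method, not as an error that invalidates the trial. Run as named and without imputation, the model leaves up to about 12 of 82 randomised participants out of the 12-month contrast and uses none of their earlier scores for it. Power is protected.

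The possible bias is roughly 0.05 to 0.2 points on a 1.0-point target. It rests on three assumptions: about 15% missing at 12 months, loss that depends on earlier SPPB differently by arm, and a total SD of 1.48 with correlations of 0.5 to 0.8 between visits. With random loss, or the same pattern within each arm, the bias is nil and a mixed model is only slightly more precise (standard error 1% to 5% smaller with random or equal loss). The documents fix neither the size nor the direction.

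**What to change.** Analyse SPPB and the other continuous outcomes with a linear mixed model for repeated measures: baseline score, arm, visit, arm-by-visit and baseline-by-visit, with unstructured covariance. Include all randomised participants with any follow-up visit. Name the primary visit and report the arm contrast there. Keep the baseline-adjusted ANCOVA as a sensitivity analysis, and add a sentence saying how participants without outcomes enter the intention-to-treat analysis.

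Optionally, analyse fallers by a method that carries partial follow-up, such as time to first fall, alongside logistic regression.

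The cost is a change of wording and slightly more modelling work, with no new data. The mixed model relies on loss being at random given the observed visits. It does not recover participants with no follow-up visit, and it does not remove bias from loss driven by an unobserved decline.

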#### Secondary outcomes

*Physiological risk of falls* will be measured by the Profile Physiological Assessment long version (PPA) [22, 23] which provides an overall score for risk of falling through a series of tests that evaluates the systems involved in the postural stability system. The results are computed using software specifically developed for the test that generates a report assessing the risk of falls. Physiological PPA tests include:○ Vision: low and high contrast, visual acuity and contrast sensitivity evaluated by the Melbourne Edge Test;○ The peripheral sensation tests: tactile sensitivity, measured by Semmes-Weinstein-type pressure esthesiometer;○ Proprioception: position sense of lower limbs;○ Muscle strength test: the muscle groups flexor and extensors of knee and ankle dorsi flexors will be assessed through a dynamometer;○ Reaction time test: Reaction time is measured in milliseconds using a modified computer, a mouse is used for response to finger pressure task and one pedal pressure for feet task;○ Balance test through a portable stabilogram, the swaymeter.

*Functional performance* measured by the self-reported WHO Disability Assessment Schedule (WHODAS 2.0) [24]. This scale measures health and functionality in 6 domains: cognition, mobility, self-care, interpersonal relationships, daily activities and participation. It was developed by WHO based on the International Classification of Functioning, Disability and Health (ICF), and it is not intended for any specific health condition. This short version assesses the difficulty degree of performing 12 activities in past 30 days, which can be classified as none, mild, moderate, severe and extreme (cannot be performed). The degree of difficulty reported is based on the presence of increased effort, discomfort or pain, slowness or the presence of some change in the way of doing the activity.

*Quality of life* measured by WHOQOL-bref [25], consists of 26 questions divided in 4 domains: physical, psychological, social relationships and environment. The questionnaire is based on the last 2 weeks of the participant and evaluated, for example, how safe he/she feel in her/his daily life and how satisfied is he/she with his/her ability to perform daily life activities.

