*Physical activity level* will be measured by the self-reported Incidental and Planned Exercise Questionnaire - IPEQ_W [26], ten questions designed to measure physical activity planned and unplanned for older people. The version estimates the intensity of physical activity during the last week will be used. The participant will be questioned for the frequency (every day, 3–6 times per week, twice a week, once a week or less than once per week) and duration of activity (less than 15min per day, more than 15min and under 30min per day, more than 30min and less than 1h, less over 1h and 2h per day more and less than 4h per day 2h, 4h, and daily or more). The total score is derived by multiplying the frequency categories by categories of activity duration, expressed in hours per week.

*Occurrence of falls* will be assessed by monthly phone calls to participants who will be encouraged to use to diary to record the number of falls each day. A structured questionnaire will be used to identify possible falls and their consequences. The intervention group will be compared to control group at 6 and 12 months follow-up in relation to the number of falls (primary outcome) and the proportion of fallers.

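### No baseline covariate is stated for either falls analysis, although a fall-risk score is measured at baseline: adding it is a free but possibly small gain in precision

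*Protocol article*

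**What the plan says.** The Statistical analysis section of the protocol article names three kinds of model.

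- **Continuous outcomes**, including physiological risk of falls: the comparison "will be performed using linear models (General Linear Models-ANCOVA) adjusted for baseline values".
- **Fall rate:** "The rate of falls will be compared between groups using negative binomial regression".
- **Dichotomous outcomes:** "Logistic regression models will be used to compare dichotomous variables between groups".

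Only the first mentions a covariate. Under Secondary outcomes, the groups are to be compared at 6 and 12 months "in relation to the number of falls (primary outcome) and the proportion of fallers", so falls enter both the second and the third kind of model.

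The same section describes the PPA as an instrument that "provides an overall score for risk of falling through a series of tests". The Outcomes section schedules all assessments "at baseline and after 3, 6 and 12 months of randomization", and Trial design places allocation after the baseline assessment. A fall-risk score will therefore exist for participants before they are randomized.

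**The concern.** A baseline variable that predicts the outcome can sharpen a randomized comparison if it enters the model. The article uses this for its continuous outcomes and does not state it for falls. Falls have no baseline value of their own in the article: they are counted prospectively, and fall history is not among the items under Sample characterization. The PPA score is the obvious substitute, since the article itself presents it as a measure of fall risk.

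Precision is scarce for this outcome. The sample size rests on the Short Physical Performance Battery (SPPB) alone, fall counts are usually overdispersed, and the article names no stratification factor that would balance fall risk between arms. What is at stake is the width of the interval around the fall rate ratio, and how far a chance difference in baseline risk can move the estimate.

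**Working it through.** **1. The plan's own figure.** The only sample-size figure concerns the SPPB: difference 1.0, SD 1.48, power 80%, significance level 5% (two-sided assumed).

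- n per arm = 2 × (1.960 + 0.842)² × 1.48² / 1.0² = 34.4, rounded up to 35.
- With 15% loss: 35 / 0.85 = 41.2, rounded up to 42; or 35 × 1.15 = 40.25, rounded up to 41.

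The stated 41 per group is reproduced to within one participant. It does not depend on the falls model, and the article gives no corresponding figure for falls. Everything below therefore rests on assumed inputs.

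**2. Gain in the rate model, by simulation.** Assumptions: 41 per arm, 1.0 to 1.5 falls per person-year, residual dispersion 0.5 to 1.0, rate ratio 0.65. Gamma-Poisson counts were generated with a standard normal covariate standing in for PPA. A negative binomial model was fitted with and without that covariate, and

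gain = (median SE unadjusted / median SE adjusted)² − 1,

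which is the equivalent percentage increase in participants.

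| Fall rate per SD of PPA | Gain | Gain, separate run |
|---|---|---|
| 1.3-fold | 2–4% | 3–4% |
| 1.5-fold | 8–12% | 7–10% |
| 2.0-fold | 20–32% | 18–34% |

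The two columns show the simulation noise. Example (1.5 falls per year, dispersion 1.0, 2.0-fold): the SE of the log rate ratio falls from 0.346 to 0.316, and (0.346 / 0.316)² − 1 = 0.20.

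**3. Cross-check by formula, under different assumptions.** With control mean μ, rate ratio 0.7 and dispersion k,

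Var(log rate ratio) = [(1/μ + k) + (1/(0.7μ) + k)] / 41,

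with PPA taken to remove a share R² of k. For μ = 1, k = 1, R² = 10%:

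- Unadjusted: (2.000 + 2.429) / 41 = 0.1080, SE 0.329.
- Adjusted (k = 0.9): (1.900 + 2.329) / 41 = 0.1031, SE 0.321, which is 2.3% lower.
- Power: 19.1% becomes 19.8%.

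Over μ 0.5 to 1.5, k 0.5 to 2 and R² 5% to 30%, the SE falls by 0.4% to 11.3%, and power rises by about 0.1 to 3.2 percentage points. In participants, the range is 1/0.996² − 1 = 1% to 1/0.887² − 1 = 27%. Both calculations start near zero and have similar upper ends.

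**4. Chance imbalance.** The difference between arms in the mean of a standardized covariate has SD √(2/41) = 0.22. An imbalance of that size multiplies the unadjusted rate ratio by 1.3^0.22 = 1.06, 1.5^0.22 = 1.09 or 2.0^0.22 = 1.17. This is the same cost as in step 2 seen from another side, not an additional one.

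**5. Scope.** These figures concern the negative binomial model only. No gain was calculated for the logistic model.

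**The case against.** The strongest objection is that the article is silent rather than wrong. It is a condensed account, and the covariates of a count model are commonly left to a full protocol or analysis plan, which is not at hand. A reader might infer from adjacent sentences, one with adjustment and one without, that the falls model will be unadjusted. The text does not say so, and that part of the objection stands. It does not remove the suggestion, which names a specific covariate already being collected.

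The different treatment is also coherent: the continuous outcomes are adjusted for their own baseline, and falls have none. Using PPA would be a choice of a different, prognostic variable. This stands too, and is why the point is an improvement and not a contradiction.

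Three stronger readings are tempting and not supported.

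- *The fall-rate model is singled out as the only one without adjustment.* It is not; the logistic models also state no covariate.
- *The unadjusted rate ratio would be biased.* Randomization makes it valid, and chance imbalance is part of the variation that its standard error already reflects.
- *PPA is a strong predictor of falls here, so much precision is thrown away.* The article says only that PPA gives a fall-risk score; it reports no association with fall counts. The upper end of the range needs a doubling of the rate per SD.

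Finally, the label of number of falls as a primary outcome sits under Secondary outcomes. It may deserve clarification, but it does not bear on the choice of covariates.

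**Conclusion.** The point holds as a free improvement of low weight. No baseline covariate is stated for either falls analysis, and a relevant one is scheduled before randomization. For the fall rate, adjustment is worth roughly 2% to 32% more participants if there are 1.0 to 1.5 falls per person-year, dispersion is 0.5 to 1.0 and the rate rises 1.3- to 2.0-fold per SD of PPA. None of these inputs comes from the documents, so the true gain is unknown and may be close to nothing. Adjustment would not rescue the falls comparison: in every case calculated by the formula in step 3, power stays below one third (highest value 32.3%). No error, bias or invalid test is shown, and the SPPB sample size is unaffected.

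**What to change.** Before unblinding, add one line to the analysis text: the baseline PPA overall score enters as a continuous covariate in the negative binomial model for the fall rate and in the logistic model for the proportion of fallers, at both 6 and 12 months. If the full analysis plan already specifies this, confirming it is enough.

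Two details belong with that line. First, state how a missing baseline PPA score is handled, so that no randomized participant drops out of the intention-to-treat comparison for want of a covariate. Second, note that the adjusted odds ratio for fallers is conditional on PPA and is not the same quantity as the crude one, so the report should say which is shown.

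The cost is a sentence or two of text and one parameter per model. No new data are needed, and a baseline question on fall history need not be added for this purpose.

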## Discussion

Several studies have found exercise in the late phase of recovery after hip fracture to be effective in improving mobility, balance [14, 15] and muscle strength [7, 14, 15]. However no previous studies have been conducted in low- and middle-income countries (LMICs). This study aims to evaluate the effectiveness of a physical exercise program in a later stage of recovery after fall-related hip fracture in improving functional mobility in older people when compared with usual care. If a positive effect is observed, this study will contribute to increase the evidence about the functionality of the therapeutic exercise program to be tested, functional training focusing on the progressive balance and resistance training of lower limb.

In LMICs the impact of ageing population and the burden of non-communicable diseases and injuries will be very significant in coming years. The evaluation of the effectiveness of an exercise program in late rehabilitation after hip fracture is substantially important in health care settings in these countries where the provision of rehabilitation after hip fracture in acute and sub-acute phases is extremely variable and restricted. Although in Brazil the hip fracture has been chosen as a sentinel event for falls in the elderly [33], the establishment of a pathway of care after hip fracture is still nascent and fragmented, with negative consequences for efficiency and equity access to rehabilitation. There is a need to organize a continuum of structured networks through integrated care health care, ensuring the transition from hospital to home care and outpatient.

We are proposing a home-based exercise program, which may in part overcome some barriers for rehabilitation, such as difficulties with public transportation and lack of a caregiver to accompany older patients to sessions. Although the program are supported by supervision on a regular basis, we believe that the visits distribution along the follow up will help patients to cope with the exercises, particularly those who are illiterate or less motivated. If proven to be effective this program may be incorporated into the public health system and contribute to building a pathway of care for older people with hip fracture.
